## Abstract

**Background:**

Parkinson disease (PD), a progressive neurodegenerative disorder, lacks disease-modifying treatments. Current therapies focus on symptomatic relief, highlighting the need for adjunctive neuroprotective strategies. Ayurveda, a holistic system, shows promise in improving PD clinical outcomes.

**Objective:**

This assessor-blinded randomized controlled study aims to systematically evaluate the efficacy of an add-on Ayurveda therapeutic regimen compared to conventional treatment as usual (TAU) in improving the clinical outcomes of PD.

**Methods:**

A total of 80 patients with PD, diagnosed according to UK Parkinson’s Disease Society Brain Bank criteria, will be randomized into two groups: TAU and add-on Ayurveda. The intervention group will receive Ayurvedic therapy alongside conventional treatment for 180 days, whereas the control group will continue TAU. Assessments will occur at baseline and at 60-, 120-, and 180-day follow-ups, evaluating motor and nonmotor symptoms. Transcranial magnetic stimulation, heart rate variability, and pulmonary function tests will assess cortical excitability, autonomic function, and pulmonary function, respectively. Immunological parameters, including cytokine levels and telomere length, will be analyzed at baseline and at 180 days to explore disease-modifying effects. Liver and renal function tests will monitor safety.

**Results:**

As of 2025, a total of 259 patients with PD have been screened for eligibility, of whom 58 participants have been successfully enrolled in the trial. Among these, 33 participants have completed the intervention and follow-up assessments, 14 have discontinued participation, and 11 are currently continuing participation in the study. Recruitment and follow-up are ongoing, and the trial is scheduled for completion in September 2026.

**Conclusions:**

This study aims to address the lack of mechanistic evidence and robust data on Ayurveda in PD. By systematically evaluating clinical efficacy and potential biomechanisms, the findings will provide preliminary evidence for Ayurvedic interventions, potentially paving the way for their integration into comprehensive PD management.

## Introduction

### Background

Parkinson disease (PD), a progressive neurodegenerative disorder characterized by motor symptoms such as tremor and rigidity, affects diverse populations worldwide [1]. First described in 1817, PD’s prevalence increases with age, impacting approximately 1% of individuals aged >65 years [2,3]. Regional variations in prevalence exist. Indian studies show a crude prevalence of 14.1 per 100,000 in rural Kashmir, with rates rising to 247 per 100,000 in those aged >60 years [4]. Conversely, Bangalore reported a lower crude prevalence of 27 per 100,000 [3]. Notably, a higher rate of 328.3 per 100,000 was observed among the Parsi community in Mumbai [5]. Early-onset PD, occurring before the age of 40 years, accounts for 3% to 5% of cases, and PD is generally twice as common in men [6]. Beyond motor symptoms, PD presents nonmotor challenges such as sleep disturbances and cognitive impairment. Autonomic dysfunction also increases with age and disease progression. Patients face a 6-fold increased risk of dementia [7].

Standard PD treatment focuses on symptom management using medications such as levodopa and dopamine agonists [8]. However, these treatments do not halt disease progression and can cause side effects [9,10]. Invasive procedures such as deep-brain stimulation are expensive and inaccessible to many, particularly in India. Consequently, many patients with PD explore complementary and alternative medicine (CAM), including Ayurveda [11]. Studies indicate that nearly half of patients with PD use CAM, typically educated, younger, urban individuals with longer disease duration [11].

While CAM, including Ayurvedic interventions, shows potential for improving motor function, robust clinical evidence is lacking. Existing research consists of limited clinical trials, pilot studies, and case reports. A systematic review of published clinical trials evaluating Ayurvedic interventions in PD suggests that therapies such as Mucuna pruriens and various Panchakarma procedures may offer potential benefits in symptom management [12]. However, the evidence is insufficient to reach any reliable conclusion. There is a need for randomized controlled trials (RCTs) with objective measures to evaluate the mechanisms of Ayurvedic treatments. Specifically, the impact of comprehensive Ayurvedic therapies on cortical activity, neuroimmune function, autonomic function, telomere length, and neuropsychological function remains unexplored. Investigating these areas will provide crucial evidence for the efficacy and safety of Ayurveda in PD and shed light on the neurobiological basis of its effects.

### Ayurveda and PD

PD can be comprehended within the paradigm of Vāta Vyādhi (neurological disorders) as delineated in Ayurveda. It is primarily attributed to Vāta Dosha Prakopa (vitiation of Vata Dosha, a bodily humor that is primarily associated with movement), which manifests as tremors, rigidity, and bradykinesia. The chronicity and progressive nature of the disease necessitate a multidimensional therapeutic approach involving Vāta-pacifying strategies, Rasāyana (rejuvenating measures), and Panchakarma (detoxification therapies) for symptomatic relief and improving disease progression [13].

### Objectives

This assessor-blinded randomized controlled study aims to systematically evaluate the efficacy of an add-on Ayurveda therapeutic regimen compared to conventional treatment as usual (TAU) in improving the clinical outcomes of PD.

The secondary objectives are to explore the effects of add-on Ayurveda therapy in comparison to conventional TAU on multiple physiological and functional parameters, namely cortical excitability, assessed through single (motor threshold [MT], resting cortical, and silent period [SP]) and paired pulse (short intracortical inhibition [SICI], long-interval cortical inhibition [LICI], and intracortical facilitation [ICF]) transcranial magnetic stimulation (TMS) measures; and immune parameters, including Th1/Th2/Th17/T-regulatory cell population, plasma C-reactive protein, plasma levels of Th1/Th2/Th17 pathway cytokines, and telomere length.

### Hypothesis

This study hypothesizes that Ayurveda treatment, when integrated with standard TAU, will be safe and effective in improving clinical and cognitive outcomes in patients with idiopathic PD. It is expected that these therapies will enhance the optimal response to levodopa, potentially leading to better symptomatic control. Ayurveda interventions are hypothesized to modulate cortical excitability measures, which will correlate with improvements in both clinical and cognitive parameters. Furthermore, it is postulated that add-on Ayurveda therapies may induce a significant shift in the Th1/Th2/Th17/T regulatory cell population, along with alterations in plasma levels of pro-inflammatory cytokines and telomere length, which will further correlate with clinical, cognitive, and neurophysiological outcomes. Finally, it is anticipated that autonomic dysfunction, as measured through heart rate variability (HRV), will show significant improvement following Ayurveda interventions, aligning with overall clinical benefits observed in patients with PD.

## Methods

### Study Design Description

This study is designed as an assessor-blinded RCT to be conducted at the National Institute of Mental Health and Neurosciences (NIMHANS), Bengaluru. The study protocol was developed collaboratively by investigators from the NIMHANS and the Central Council for Research in Ayurvedic Sciences (CCRAS) based on existing clinical and preclinical evidence, and it underwent expert peer review before funding approval.

### Trial Design

This study is a prospective, assessor-blinded, exploratory RCT with a parallel-group design and a 1:1 allocation ratio. It is designed as a superiority trial to evaluate the potential benefits of an Ayurvedic therapeutic regimen as an add-on to optimized conventional management in patients with PD, compared to optimized conventional management alone. The trial will be conducted at a single tertiary care center (NIMHANS, Bengaluru, India) over a period of 3 years (Figure 1).

**Figure 1. F1:**
[figure not shown]
Study design. TAU: treatment as usual.

Participants will be followed for 24 weeks post-randomization. The study aims to generate preliminary evidence on clinical efficacy and mechanistic insights related to cortical excitability, neuroimmune function, and autonomic function. Participants will be randomized into either the add-on Ayurveda intervention arm or the TAU control arm, with each participant undergoing a 6-month study period.

Participants will be recruited from both the outpatient department (OPD) and inpatient department services of the Departments of Neurology and Integrative Medicine at the NIMHANS, Bengaluru, India. NIMHANS is a tertiary care neuropsychiatric and neurosciences hospital and Institute of National Importance under the Ministry of Health and Family Welfare, Government of India. The study will be conducted within NIMHANS using its specialized neurology and integrative medicine infrastructure for recruitment, intervention delivery, and follow-up assessments.

Those meeting the inclusion criteria will be recruited after obtaining written informed consent. Informed consent will be obtained by the senior research fellow (SRF) possessing an MD (Ayurveda) qualification, who has been trained in Good Clinical Practice (GCP) [14] and institutional ethical guidelines for human research. The study procedures, potential benefits, risks, and the right to withdraw at any stage will be clearly explained in the patient’s language, and a copy of the consent document will be provided (Multimedia Appendix 1).

To promote adequate enrollment, participants will be recruited through advertisements in print and institutional media, as well as by prescreening of hospital health records to identify potentially eligible individuals. Efforts will also be made to minimize participant burden by providing clear information, convenient scheduling of assessments, and coordinated support from study staff during recruitment and follow-up.

### Selection of Participants

#### Inclusion Criteria

Participants eligible for the study will be those diagnosed with Idiopathic PD based on the UK Parkinson’s Disease Society Brain Bank criteria [15]. The study will include individuals in Hoehn and Yahr stages 2.5 to 4, with a disease duration of more than 3 years, experiencing severe motor fluctuations and suboptimal response to standard treatment, including dyskinesia and gait freezing. The eligible age range for participation will be 40 to 70 years. Participants must be on a stable dopaminergic regimen for ≥2 weeks before baseline.

#### Exclusion Criteria

Participants with Parkinsonism spectrum disorders or other neurodegenerative conditions, such as motor neuron diseases and multiple sclerosis, will be excluded from the study. Individuals with major cardiovascular disorders or those with hepatic, renal, or uncontrolled pulmonary dysfunction will not be eligible. Patients receiving concomitant medications that may interfere with Parkinsonian symptoms, including anticoagulants, neuroleptics, metoclopramide, Compazine, beta-blockers, fluoxetine, clozapine, quetiapine, olanzapine, buspirone, antipsychotics, and central nervous system stimulants such as sodium valproate, will also be excluded. Those with cognitive impairment, defined by a Mini-Mental State Examination score of <18, as well as individuals with evidence of malignancy or a history of substance abuse, will not be considered for participation. Additionally, patients who have participated in any other clinical trial within the past 6 months will be excluded to ensure unbiased study outcomes.

### Sample Size

This study has been designed as an exploratory trial primarily aimed at assessing feasibility and generating preliminary clinical evidence on the effects of a multicomponent Ayurvedic add-on therapy in PD. The sample size estimation was based on parameters from a prior exploratory study [16], which reported a mean change in the Unified Parkinson’s Disease Rating Scale (UPDRS) score of 1.0 with an SD of 2.0 and a correlation coefficient of 0.60. Using these assumptions, a 2-tailed alpha of 0.05, and 80% power, the required sample size was calculated to be 28 participants per group. Allowing for a 20% attrition rate, a total of 40 participants per group (80 overall) will be recruited.

This sample size is expected to provide preliminary insights into the effects of add-on Ayurveda therapy in PD and to serve as a basis for future large-scale confirmatory trials.

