### Outcome Measures

The primary outcome is the change in the total score of the Movement Disorder Society-UPDRS (MDS-UPDRS) after 6 months of treatment, compared with the baseline. MDS-UPDRS Part III will be assessed in both the ON and OFF medication states. The OFF state assessment will be conducted after a 12-hour withdrawal from the patient’s last dopaminergic medication, whereas the ON state assessment will be performed 1 hour after the administration of the first morning dose of dopaminergic medication. The OFF-state evaluation (after 12 h withdrawal) reflects the underlying disease severity, whereas the ON-state evaluation (1-h postmorning dose) reflects treatment responsiveness. The total MDS-UPDRS change is thus intended to integrate both clinical states, which is relevant for this exploratory phase of the Ayurvedic add-on intervention assessment.

The secondary outcome measures include a range of neurophysiological, biochemical, cognitive, and functional parameters. Cortical excitability will be assessed using TMS, evaluating both single-pulse (MT, resting cortical, and SP) and paired-pulse (SICI, LICI, and ICF) measures. Autonomic function will be analyzed through HRV, whereas pulmonary function tests will assess respiratory capacity.

Exploratory mechanistic outcomes include alterations in immunological markers, including changes in Th1/Th2/Th17/T regulatory cell populations, plasma levels of pro-inflammatory cytokines, and telomere length, which will be measured to evaluate the immunomodulatory and anti-inflammatory effects of the intervention.

Functional and motor outcomes will be examined through reductions in dyskinesia severity using the Unified Dyskinesia Rating Scale and improvements in gait parameters, measured using the 6-minute walk test and gait speed (10-m walk test). Cognitive function will be assessed using the Montreal Cognitive Assessment, and postural stability will be evaluated through the Balance Error Scoring System. Changes in Scales for Outcomes in Parkinson’s disease-Sleep will be monitored to assess improvements in sleep disturbances associated with PD.

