### Brief Description of Some Relevant Assessments

#### Clinical Assessments

##### Movement Disorder Society–Unified Parkinson’s Disease Rating Scale

This scale assesses motor and nonmotor PD symptoms. It includes four parts: nonmotor experiences of daily living (part I), motor experiences of daily living (part II), motor examination (part III), and motor complications (part IV). Parts IA, IB, and II are conducted in the “ON” state, whereas Part III is assessed in both “ON” and “OFF” states. Part IV integrates patient-reported information with clinical observations [18].

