### Statistical Analysis

All analyses will be performed using SPSS software. The primary outcome, change in MDS-UPDRS Part III score from baseline to 24 weeks, will be analyzed using a mixed model for repeated measures with treatment, time, and treatment×time interaction as fixed effects and baseline values as covariates. LEDD will be included as a time-varying covariate to account for dopaminergic medication effects. Results will be reported as least-square mean differences with 95% CIs. The main analysis will follow a modified intention-to-treat approach including all randomized participants who receive at least one dose of the assigned intervention, whereas a per-protocol analysis will be performed as a sensitivity check on participants who complete ≥80% of scheduled therapies and medication adherence.

Missing data will be handled under the assumption of data missing at random using the mixed model for repeated measures model, which uses all available data without imputation. Additional sensitivity analyses, including multiple imputation and complete case analyses, will be performed to evaluate the robustness of results. The secondary outcomes will be analyzed using appropriate mixed or generalized linear models and interpreted as exploratory. Descriptive statistics will summarize categorical variables as frequencies and percentages, and continuous variables as mean (SD), median (IQR), and range.

Predefined subgroup analyses will explore whether treatment effects differ by baseline Hoehn and Yahr stage (≤3.0 vs >3.0), disease duration (<5 vs ≥5 y), age (<65 vs ≥65 y), baseline LEDD (≤ median vs >median), and presence of dyskinesia. Interaction terms will be tested using mixed effects models, and the results will be interpreted as exploratory. Sensitivity analyses will include assessing participants with stable dopaminergic doses (<10% LEDD change) and testing the interaction between treatment allocation and LEDD change to explore medication-dependent effects. Safety analyses will be descriptive, summarizing AEs and serious AEs by treatment group.

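### The stated 80% power rests on a 1.0-point change (SD 2.0) on an unspecified UPDRS score, so it is not shown for the MDS-UPDRS primary outcome, whether total or Part III

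*Protocol article*

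**What the plan says.** All references are to the protocol article.

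- **Sample Size.** The inputs come from a prior exploratory study, "which reported a mean change in the Unified Parkinson’s Disease Rating Scale (UPDRS) score of 1.0 with an SD of 2.0", together with a correlation of 0.60. With "a 2-tailed alpha of 0.05, and 80% power", "the required sample size was calculated to be 28 participants per group". Then: "Allowing for a 20% attrition rate, a total of 40 participants per group (80 overall) will be recruited". The section does not say which version or part of the scale is meant, in which medication state or at what time point. Nor does it say whether 1.0 is a change within one group or a difference between groups.
- **Outcome Measures.** "The primary outcome is the change in the total score of the Movement Disorder Society-UPDRS (MDS-UPDRS) after 6 months of treatment". The same section says that the total is meant to combine the ON and OFF states.
- **Statistical Analysis.** "The primary outcome, change in MDS-UPDRS Part III score from baseline to 24 weeks", analysed by a mixed model for repeated measures with baseline as a covariate. The Harms section also names Part III as the primary outcome.
- **Description of the MDS-UPDRS.** The scale has four parts, and "Part III is assessed in both “ON” and “OFF” states".
- **Trial Design.** A 1:1 parallel-group superiority trial, also labelled exploratory.

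**The concern.** A difference and an SD in raw points have meaning only for the score they were measured on. Here the planning score is not identified, and the article gives two descriptions of the outcome it is meant to serve. A change SD of 2 points might suit one score, but it cannot be taken to hold for a four-part total, for Part III ON and for Part III OFF alike. The eligible patients are at Hoehn and Yahr 2.5 to 4 with marked motor fluctuations, and the OFF rating follows a 12-hour withdrawal, so how far the score varies in them matters for the calculation.

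The stake is how the result is read. A reader who accepts the 80% figure could take a non-significant result as evidence against a 1.0-point effect. The article also presents the trial as a basis for later confirmatory trials, whose planners need a difference and an SD attached to a named score.

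**Working it through.** **1. Reproducing 28.** Inputs from Sample Size: difference 1.0, SD 2.0, r = 0.60, two-sided alpha 0.05, power 80%. Read the SD as that of a single measurement.

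- SD of change = 2.0 × √(2 × (1 − 0.60)) = 1.789.
- One-group paired test, normal approximation: (1.960 + 0.842)² × 1.789² / 1.0² = 7.849 × 3.2 = 25.1.
- Exact paired t: 27.1, rounded up to **28** (power 81.4% at n = 28).

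So 28 is the size for a before-after test within one group.

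**2. The between-arm comparison on the same inputs.** Required n per arm = 2 × 7.849 × SD² / 1.0² (normal approximation). Power is from the two-sample t-test.

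| SD used | n per arm for 80% | Power at 28 | Power at 32 |
|---|---|---|---|
| 2.0 (unadjusted) | 63 | 45% | 50% |
| 1.789 (change score, r = 0.60) | 51 | 54% | 60% |
| 2.0 × √(1 − 0.60²) = 1.6 (baseline-adjusted) | 41 | 63% | 69% |

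Averaging three post-baseline visits with baseline adjustment, under compound symmetry, would need about 24 per arm. That is not 28 either, and the primary outcome is the change at 6 months, not an average over visits. These shortfalls come from the formula, not from the scale.

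**3. Setting the scores side by side.** The planning score is a UPDRS score with nothing further specified. The outcome is the MDS-UPDRS total (Outcome Measures) or MDS-UPDRS Part III (Statistical Analysis, Harms), with Part III rated in two states. The article defines the two abbreviations separately and gives no link between the planning figures and either outcome. Correcting the formula in step 2 would not change this.

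**4. What the planned size can detect on any score.** Solving the two-sample t-test for 80% power:

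- 28 evaluable per arm: 0.762 SD.
- 32 evaluable per arm: 0.711 SD.

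The figure 32 is 40 × (1 − 0.20). The figure 28 is the stated requirement and also corresponds to 30% loss (40 × 0.70). The Results section reports 33 completed and 14 discontinued, so 14/47 = 30% of those with a known outcome were lost.

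Under the planned analysis, the SD to use is that of the day-180 change after baseline adjustment. The documents give no such SD for any MDS-UPDRS score. **Assumed** values for illustration, 28 per arm:

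| Assumed residual SD | Detectable difference (points) | Power for 1.0 point |
|---|---|---|
| 4 | 3.0 | 15% |
| 8 | 6.1 | 7.5% |
| 12 | 9.1 | 6% |

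**The case against.** **The source is unseen.** The cited study is not at hand. UPDRS may be loose shorthand there for the MDS version or for one part. This stands. A reader might infer that the power was computed for a different endpoint or on the wrong scale, but the documents do not establish that. They show only that the score is not identified and that the outcome is described in two ways.

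**The size of the effect is partly assumed.** This also stands. The fall from 80% to 45% at SD 2.0 comes entirely from using a two-group formula, and the SDs of 4 to 12 are not in the documents. An unadjusted test is also not the planned one. Baseline adjustment raises 45% to 63% on the stated inputs, which is still below 80%.

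**A null result will be read from its confidence interval.** The plan promises 95% CIs, so precision will be visible. It would be wrong to say that the trial can exclude only differences as large as the detectable one. At an assumed SD of 8 with 28 per arm, the detectable difference is 6.1 points, while the CI half-width is about 2.005 × 8 × √(2/28) = 4.3 points.

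**The trial is exploratory, and an article condenses its protocol.** The label lowers the weight of the point. It does not make a stated 80% power correct, and the article also calls the trial a superiority trial. The point concerns a figure that the article prints, not a justification that it leaves out.

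**Conclusion.** The point holds in a limited form. The article asserts 80% power from raw-point inputs on an unidentified score, and its primary outcome is either of two MDS-UPDRS scores. The 80% is therefore not shown for the primary endpoint, whichever is meant.

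Even if the inputs did belong to the right score, power for a between-arm difference of 1.0 would be about 45% unadjusted or 63% baseline-adjusted at 28 per arm. Both figures take 2.0 as the SD of a single measurement, and the second uses r = 0.60. If 2.0 is instead the SD of change, the single-measurement SD is 2.0/√0.8 = 2.236, the adjusted SD is 2.236 × 0.8 = 1.789, and the adjusted power is about 54%.

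Powers of 6% to 15% should not be read as the trial's actual power, since they depend on assumed SDs. Nor does the point show that 80 participants are too few for an exploratory trial. It calls for a corrected statement of precision, not a larger trial.

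**What to change.** 1. Settle the primary score first: total or Part III, and the medication state. Use the same definition in Outcome Measures, Statistical Analysis and Harms.
2. Keep n = 80. In Sample Size, remove the claim of 80% power for a 1.0-point (SD 2.0) UPDRS change.
3. Replace it with a statement such as: *With 28 (32) evaluable participants per arm, the trial has 80% power for a between-arm difference of about 0.76 (0.71) SD in change in [named score, named state] at day 180, where the SD is that of the change after baseline adjustment.*
4. Convert to points with a pooled residual SD of that same score and state from data already collected: regress day-180 change on baseline with no arm term and no look by arm, coded or otherwise. State that it comes from completers (33 as of August 2025). It also absorbs any true arm difference. At 0.76 SD and equal arms, the inflation is about √(1 + 0.76²/4) = 1.07, so the result errs slightly on the cautious side.
5. If the prior study's figures are kept as background, name the scale version, part, state and time point they refer to.
6. Document the change as an amendment, since 58 participants are already enrolled.

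The cost is a decision on the primary score, a rewritten paragraph, one pooled calculation and an amendment record. No patients or procedures are added. The stated power becomes less favourable.

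### 28 per group does not give 80% power for the planned between-arm comparison; on the stated inputs a 1.0-point difference needs 42 to 64 per arm

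*Protocol article*

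**What the plan says.** The Sample Size section of the protocol article draws on a prior exploratory study for a mean change in UPDRS "score of 1.0 with an SD of 2.0 and a correlation coefficient of 0.60". It then concludes: "Using these assumptions, a 2-tailed alpha of 0.05, and 80% power, the required sample size was calculated to be 28 participants per group". Recruitment is set above that: "Allowing for a 20% attrition rate, a total of 40 participants per group (80 overall) will be recruited".

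The section names no test or formula. It does not say whether 1.0 is a change within one group or a difference between arms, whether 2.0 is the SD of the score or of the change, or which two measurements the correlation links.

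The Trial Design section describes an "exploratory RCT with a parallel-group design and a 1:1 allocation ratio" and continues: "It is designed as a superiority trial to evaluate the potential benefits of an Ayurvedic therapeutic regimen as an add-on". The Statistical Analysis section plans a mixed model for repeated measures with treatment, time, their interaction and baseline as covariate, reported as least-square mean differences with 95% CIs. The question the trial answers is therefore a contrast between arms. The Sample Size section also calls the study exploratory and directed mainly at feasibility and preliminary evidence.

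**The concern.** A correlation belongs naturally in a before-after calculation, and 28 is small for a standardised effect of 1.0/2.0 = 0.5 in a two-arm trial. If 28 comes from a before-after test in one group, it answers whether patients change from their own baseline, not whether add-on Ayurveda does better than usual treatment.

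What is at stake is the stated power. A reader who takes 80% at face value will give a null between-arm result more weight than it can bear. A later confirmatory trial, which the article says this one should inform, could also inherit the same calculation.

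**Working it through.** **Inputs** (Sample Size section): difference 1.0; SD 2.0; correlation r = 0.60, read as baseline to follow-up; two-sided alpha 0.05; power 80%; 40 recruited per arm; 20% attrition. Power is from the noncentral t distribution.

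**Step 1: reproduce 28.** One-group paired t-test:

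- SD of change = 2.0 × √(2 × (1 − 0.60)) = 2.0 × √0.8 = 1.789
- standardised change = 1.0 / 1.789 = 0.559
- power = 79.8% at n = 27 and 81.4% at n = 28

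The smallest n that reaches 80% is 28, an exact match that uses every stated input.

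**Step 2: the two-arm comparison at 6 months.** For a between-arm difference of 1.0, n per arm ≈ 2 × (1.960 + 0.842)² × SD² = 15.70 × SD², then refined with the t distribution. The SD depends on how the inputs are read:

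- Baseline-adjusted: 2.0 × √(1 − 0.60²) = 1.600. Approximation 40.2, exact 42.
- Change scores, with 2.0 as the raw-score SD: 1.789. Approximation 50.2, exact 52.
- 2.0 as the SD of change itself: 2.000. Approximation 62.8, exact 64.

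Power for 1.0 point, by evaluable number per arm (40 × 0.80 = 32):

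| Reading | n per arm for 80% | 28 | 32 | 40, no loss |
|---|---|---|---|---|
| Baseline-adjusted | 42 | 63% | 69% | 79% |
| Change scores | 52 | 54% | 60% | 69% |
| 2.0 = SD of change | 64 | 45% | 50% | 60% |

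Between-arm difference detectable with 80% power:

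| Reading | 28 per arm | 32 per arm |
|---|---|---|
| Baseline-adjusted | 1.22 | 1.14 |
| Change scores | 1.36 | 1.27 |
| 2.0 = SD of change | 1.52 | 1.42 |

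**Step 3: other routes to 28.**

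- *Two-arm, baseline-adjusted, mean of two follow-ups, all correlations 0.60.* The variance factor is (1 + 0.60)/2 − 0.36 = 0.44, and 15.70 × 4 × 0.44 = 27.6, so 28 (29 with the t distribution). The trial has three follow-up visits, for which the same formula gives 23.4, and the endpoint is at 6 months rather than an average.
- *Variance taken as SD² × (1 − r).* This gives 26 to 27, and it is the variance of neither a change score nor a baseline-adjusted outcome.
- *Repeated-measures group-by-time interaction with f = 0.25 and two time points.* This gives 28 in total, not per group. An f of 0.25 means a deviation of 0.25 × 2.0 = 0.5 in each of four cells, so changes that differ by 4 × 0.5 = 2.0 points between arms, not 1.0.

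None of these gives 28 per group for a 1.0-point contrast at 6 months.

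**The case against.** **The paired origin is not documented.** This is right. The article names no test, and the cited study cannot be consulted here. A reader might infer that the authors demonstrably used a paired formula, or that the 1.0 was a within-group change in that study. The text establishes neither. The shortfall in power does not depend on it, because it appears under all three two-arm readings.

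**The low figures use the least favourable readings.** Also right in part. A reader might infer that the trial has no real power, or is a coin toss. The 45% needs 2.0 to be the SD of change, no gain from baseline adjustment, and only 28 evaluable per arm. The plan adjusts for baseline and expects 32 per arm after attrition, so its nearest figure is about 69%. The mixed model may also recover a little from participants with partial follow-up. But 69% is not 80%, and even 40 per arm with no loss reaches only 79%. The Results section reports 14 of 58 enrolled participants discontinued (24%), or 14 of the 33 + 14 = 47 with a known end status (30%); a 30% loss from 40 leaves 28.

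**The trial is exploratory and already plans estimates with 95% CIs.** This softens the consequence, and a misread null result is a risk rather than a certainty. An exploratory trial did not need a power claim. This one makes one, within a superiority design, and the label does not make the figure correct.

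**Conclusion.** The point holds as a wrong power statement. On the article's own inputs, 28 per group matches a one-group paired test and no standard two-arm calculation for the 6-month contrast. For a 1.0-point difference between arms, 80% power needs 42, 52 or 64 per arm. With 28 to 32 evaluable, power is about 63% to 69% under the reading closest to the planned model and 45% to 60% under the other two.

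These figures assume that the 1.0 is meant as the between-arm difference to detect, that the correlation is between baseline and 6 months, and that the SD is equal in both arms. They stay on the UPDRS scale of the planning inputs, whereas the trial's outcome is the MDS-UPDRS; the documents give no SD for that scale.

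The finding does not show that 80 participants are too few for an exploratory trial, or that the planned analysis is unsound.

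**What to change.** Keep 80 participants and amend the Sample Size section:

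- Withdraw the statement that 28 per group gives 80% power.
- Name the test that was assumed, and say what the 1.0, the SD and the correlation each refer to.
- State that with 28 to 32 evaluable per arm the baseline-adjusted comparison has about 63% to 69% power for 1.0 point (45% to 60% under the other readings), and that the difference detectable with 80% power is about 1.1 to 1.2 points (up to 1.5).
- Express this on the MDS-UPDRS endpoint the trial will use. Outcome Measures names the total score and Statistical Analysis names Part III, so one must be fixed first. A blinded pooled SD from data in hand could support this, with the caveat that an SD from the 33 completers is imprecise and comes from a selected group.
- Interpret the result through the between-arm difference and 95% CI already planned, and do not describe it as a superiority test with 80% power.

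The cost is protocol wording and, optionally, one blinded SD calculation. No patients are added and the primary analysis does not change. The downside is a less favourable stated power.
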